## **Additional File 2**

### **Statistical Analysis Plan for the iMAP2 trial**

**Version3**

**5th May 2017**

#### **1. Introduction**

##### **1.1 Trial details**

This is the statistical analysis plan for the following trial:

*A randomised controlled trial comparing two pertussis-containing vaccines in pregnancy and vaccine responses in UK mothers and their infants  
(immunising Mums Against Pertussis, iMAP2)*

The research question is to assess antibody responses following primary immunisation in children born to mothers vaccinated in pregnancy with one of two pertussis containing vaccines (by randomisation) and also in a smaller group of children born to unvaccinated mothers. The full rationale is given in the Protocol.

##### **1.3 Changes to this analysis plan:**

A final version of this plan will be produced prior to provision of data to the statistician. Any additional analysis or deviation(s) from this analysis plan will be documented and the reasons given.

#### **2. Objectives**

##### **2.1 Primary**

**PO:** To compare anti-pertussis toxin (PT) IgG responses following primary immunisation with an acellular pertussis- containing vaccine in infants born to mothers who received REPEVAX in pregnancy compared to infants whose mothers received BOOSTRIX-IPV in pregnancy.

##### **2.2 Secondary**

###### ***Infant***

**SI1:** To compare antibody responses to pertussis antigens (concentration of IgG antibody to PT, pertactin (PRN), filamentous haemagglutinin (FHA) and fimbrial antigens 2 and 3 (FIM 2 and 3)), tetanus toxoid, diphtheria toxoid and polio serotypes 1, 2 and 3 at birth amongst infants born to mothers who received REPEVAX in pregnancy compared to infants whose mothers received BOOSTRIX-IPV in pregnancy

**SI2:** To compare antibody responses to pertussis antigens [IgG to PT, PRN, FHA and FIM 2 and 3], Hib antigen [PRP], tetanus toxoid, diphtheria toxoid and polio serotypes 1, 2 and 3; meningococcal serogroup C serum bactericidal antibody titres and meningococcal serogroup C-specific IgG concentrations; 13 serotype-specific pneumococcal IgG concentrations and functional pneumococcal antibody studies at 2, 5 and 13 months of age (just before and one month after primary immunization and one month after booster vaccines) in infants born to mothers who received REPEVAX in pregnancy compared to infants whose mothers received BOOSTRIX-IPV in pregnancy and compared to infants whose mothers who did not receive pertussis vaccination in pregnancy

### ***Mother***

**SM1:** To determine concentrations of antibodies to pertussis antigens [IgG to PT, PRN, FHA and FIM 2 and 3] and tetanus toxoid, diphtheria toxoid and polio serotypes 1, 2 and 3, in pregnant women prior to administration of the REPEVAX or BOOSTRIX-IPV vaccine and at the time of delivery

**SM2:** To estimate the placental transfer ratio of antibodies to pertussis antigens [IgG to PT, PRN, FHA and FIM 2 and 3] and tetanus toxoid, diphtheria toxoid and polio serotypes 1, 2 and 3, in mothers who received REPEVAX in pregnancy compared to mothers who received BOOSTRIX-IPV in pregnancy

**SM3:** To compare concentrations of antibodies to pertussis antigens [IgG to PT, PRN, FHA and FIM 2 and 3] and polio serotypes 1, 2 and 3 at 12-13 months post-delivery in women who received REPEVAX or BOOSTRIX-IPV vaccine and to those women who did not receive pertussis vaccination in pregnancy

## **3. Design**

Full details are in the study protocol. Briefly women will be recruited at two sites during routine antenatal appointments and randomised to receive either REPEVAX or BOOSTRIX in pregnancy. A separate group of women who did not receive vaccination in pregnancy will be recruited at post natal visits as a control group.

### **3.1 Study schedule**

| Visit                                 | V1
Pregnancy                  | V2
Birth                | V3
2 months       | V4
3 months           | V5
4 months           | V6
5 months           | V7
12 months     | V8
13 months          |
|---------------------------------------|----------------------------------|----------------------------|----------------------|--------------------------|--------------------------|--------------------------|---------------------|--------------------------|
| Visit Window                          | 28-32 weeks                      | 0-7 days hours after birth | 49-84 days of age    | 21-42 days after visit 3 | 21-42 days after visit 4 | 21-42 days after visit 5 | 353-390 days of age | 21-42 days after visit 7 |
| Vaccinated mothers:                   | REPEVAX/BOOSTRIX-IPV
Blood MA | Blood MB                   |                      |                          |                          |                          |                     | Blood MC                 |
| Unvaccinated Mothers                  |                                  |                            |                      |                          |                          |                          |                     | Blood MC                 |
| Infants born to vaccinated mothers:   |                                  | Blood BA                   | Routine*
Blood BB | Routine*                 | Routine*                 | Blood BC                 | Routine*            | (MMR**) Blood BD         |
| Infants born to unvaccinated mothers: |                                  |                            | Routine*
Blood BB | Routine*                 | Routine*                 | Blood BC                 | Routine*            | (MMR**) Blood BD         |

\*routine schedule is 2m: Infanrix/Prev13/Bexsero/Rotarix, 3m: Infanrix/MenC (Neis)/Rotarix, 4m: Infanrix/Prev/Bexsero, 12m: Menitorix/Prev/Bexsero/MMR. \*\*MMR can be given at 12m or at 13m.

### **3.2 Randomisation and blinding**

Randomisation is from a block randomisation list produced prior to the study. On recruitment to the study, each subject will be allocated, in order of inclusion, the next available subject number. The study number will define the group to which the mother is assigned and which pertussis-containing vaccine she will receive. Mothers and their infants who are recruited in the postnatal period as part of the control group will not be randomised. Laboratory staff that test maternal and infant blood samples for vaccine responses will be blinded to the group allocation. Pregnant women and other study personnel will not be blinded. Though written informed consent will be taken at the first visit, continued consent to participate will be ascertained at each subsequent visit.

#### **4. Sample Size**

Based on sample size calculations below, it is proposed that a convenience sample of 65 (+/-10) mother-infant pairs will be recruited into each of the two groups that received a pertussis vaccine in pregnancy, with a control group of 30 (+/-10) women and their infants. Up to 200 mother-infant pairs will be recruited to take account of mother-infant pairs lost to follow-up.

The sample size calculation is based on data from the recent P13UK study performed by PHE. Based on these results, the standard deviation of the post-primary vaccination GMCs (log-10 scale) was: PT = 0.28, Hib = 0.76, MenC SBA = 0.50, Tet = 0.37. Based on these SD with 65 per study arm fold differences of 1.38, 2.37, 1.77 and 1.52 would be detectable between the vaccine arms for PT, Hib, MenC and Tet respectively. In terms of percentages reaching putative protective levels 95% in one arm would be different to percentages below 77% in the other arm. The protocol has more details on other sample sizes.

#### **5. Increasing the size of the unvaccinated group**

Due to the small size of the unvaccinated arm (control group), this will be increased by including results from babies of unvaccinated mothers who participated in the Infanrix Hexa study (18 babies consenting from 2014-January 2016). These results are from testing in the same Laboratory. The schedule for infants in this study was

2m: Infanrix-Hexa™ & PCV13 & Rotarix™  
3m: Infanrix-Hexa™ & Menitorix or NeisVacc™ & Rotarix™  
4m: Infanrix-Hexa™ & PCV13  
12m: PCV13 & MMR & Menitorix™

With bloods at 4m, 5m, 12m, 13m

Children will also have received Bexsero (at 2, 4m or in a 1 or 2 dose catch up) if born from May 2015.

Therefore vaccines are the same other than hepB added as Infanrix-hexa and MenC given at 3m. For the control group Meningococcal outcomes will therefore not be assessed. The results of the other antibodies (pertussis, dip, tet, Hib, polio and pneumo) will be compared first between these 18 and the controls recruited in this study and only combined if differences are not significant at  $p < 0.005$  to allow for multiple comparisons).

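### The equivalence statement used to justify pooling 18 external infants into the control group leaves out Bexsero, which by the SAP's own schedules also differs

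*SAP*

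**What the plan says.** Section 5 adds results from "18 babies consenting from 2014-January 2016", all born to unvaccinated mothers in the earlier study, to the trial's own controls. It lists their vaccines by visit, including "3m: Infanrix-Hexa™ & Menitorix or NeisVacc™ & Rotarix™" and "12m: PCV13 & MMR & Menitorix™". Bexsero is in none of the visit lines and is covered in a separate sentence: "Children will also have received Bexsero (at 2, 4m or in a 1 or 2 dose catch up) if born from May 2015". The next sentence draws the conclusion: "Therefore vaccines are the same other than hepB added as Infanrix-hexa and MenC given at 3m".

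For trial infants, the footnote to section 3.1 reads: "routine schedule is 2m: Infanrix/Prev13/Bexsero/Rotarix, 3m: Infanrix/MenC (Neis)/Rotarix, 4m: Infanrix/Prev/Bexsero, 12m: Menitorix/Prev/Bexsero/MMR".

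Section 5 contains two safeguards. One removes outcomes: "For the control group Meningococcal outcomes will therefore not be assessed". The other tests the 18 against the trial controls on the remaining antibodies, and the two sets are "only combined if differences are not significant at" p < 0.005.

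**The concern.** The equivalence sentence is the only argument the SAP gives for treating the two sets of infants as comparable in what they were vaccinated with. It names two exceptions, and Bexsero is not one of them, although the sentence just before it shows a difference by date of birth and by number of doses.

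At stake is the secondary infant objective SI2, which compares infants of vaccinated mothers with controls. If infants of vaccinated mothers follow the section 3.1 schedule while part of the pooled control group had no Bexsero or fewer doses, exposure to maternal vaccine and exposure to Bexsero are partly confounded. Any effect of co-administered Bexsero on the pertussis, diphtheria, tetanus, Hib, polio or pneumococcal results would be counted as an effect of maternal vaccination. Dropping the meningococcal outcomes does not help with these antibodies, and Bexsero receipt is not among the covariates named in section 10.5.

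**Working it through.** **1. The two schedules side by side**

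| | Trial infants (SAP 3.1, footnote) | External infants (SAP 5) | Named as a difference in section 5? |
|---|---|---|---|
| Bexsero, 2 and 4 months | Scheduled | Only if born from May 2015; some by catch-up of 1 or 2 doses | No |
| Bexsero, 12 months | Scheduled | Not in the 12-month line | No |
| MenC product, 3 months | NeisVac | Menitorix or NeisVac | Yes, in loose wording |
| Hepatitis B | Not listed | In the hexavalent vaccine | Yes |

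The Bexsero rows are the unlisted difference. The 12-month row is weaker evidence than the first, because the external visit lines omit Bexsero at every age.

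**2. How many of the 18 may have had none**

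The SAP gives no figure to reproduce. The inputs are 18 infants, a consent window from 2014 (month not stated) to January 2016, and the May 2015 birth cut-off (all section 5). Assumptions: consent spread evenly by month, and a fixed age at consent.

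Share = (consent months whose births fall before May 2015) / (all consent months)

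| Consent starts | Months in window | Consent at birth | Consent at 2 months | Consent at 4 months |
|---|---|---|---|---|
| January 2014 | 25 | 16/25 = 64% | 18/25 = 72% | 20/25 = 80% |
| July 2014 | 19 | 10/19 = 53% | 12/19 = 63% | 14/19 = 74% |
| October 2014 | 16 | 7/16 = 44% | 9/16 = 56% | 11/16 = 69% |
| December 2014 | 14 | 5/14 = 36% | 7/14 = 50% | 9/14 = 64% |

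The range is 36% to 80%: 18 × 0.357 = 6.4 to 18 × 0.80 = 14.4, or about 6 to 14 infants.

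**3. Weight in the pooled control group**

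Section 4 plans 30 trial controls, plus or minus 10. All 18 external infants would be 18/48 = 37.5% of the pooled group (18/58 = 31% with 40 trial controls, 18/38 = 47% with 20). Those without Bexsero would be 6/48 = 12.5% to 14/48 = 29% with 30 trial controls, and 6/38 = 16% to 14/38 = 37% with 20.

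If lack of Bexsero changed a response F-fold, k such infants among N controls would move the control geometric mean by F^(k/N). For a purely illustrative F = 2 and N = 48, that is 2^(6/48) = 1.09-fold to 2^(14/48) = 1.22-fold. The SAP gives no value for F.

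**4. What the p < 0.005 check can see**

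Inputs: 18 against 30 infants and the log10 standard deviations in section 4 (PT 0.28, Hib 0.76, tetanus 0.37). These are post-primary values and are used here as an approximation. The test is a two-sided t-test at 0.005 with 46 degrees of freedom, critical value 2.95.

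Standard error = SD × √(1/18 + 1/30) = SD × 0.298

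- PT, 1.38-fold: log10 difference 0.140; SE 0.0835; noncentrality 1.68; power 11.5%.
- PT, 2-fold: 0.301 / 0.0835 = 3.61; power 74%.
- Tetanus, 1.5-fold: 0.176 / 0.110 = 1.60; power 10%.
- Hib, 2-fold: 0.301 / 0.227 = 1.33; power 6%.

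For 80% power the true difference would have to be about 2.1-fold (PT), 2.6-fold (tetanus) or 7.3-fold (Hib). The 1.38-fold PT difference is the one section 4 calls detectable between the vaccine arms. These powers also assume that all 18 differ. If only k of them do, the log difference seen by the check shrinks by k/18: a 2-fold effect confined to 6 infants appears as 2^(6/18) = 1.26-fold.

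**The case against.** The best defence is that the SAP discloses the Bexsero difference one sentence earlier, removes the meningococcal outcomes and compares results before combining. The primary endpoint (section 6.1) uses only infants of vaccinated mothers. External infants have no 2-month sample, so only the 5- and 13-month contrasts are touched, and those are with a non-randomised group in any case. Nothing in the SAP says that Bexsero changes the antibodies that remain pooled. All of this stands, and it limits the point to a secondary comparison and a possible, not demonstrated, bias. It does not make the equivalence sentence correct, and the low power of the check means that passing it is little reassurance.

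Four stronger readings are tempting and not supported:

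- **That a condition for entering the control group is false.** Vaccine equivalence is offered as a rationale. The only stated condition for combining is the p < 0.005 comparison.
- **That at least half of the 18 had no Bexsero.** Many even-consent scenarios give that, but not all do, and the start month, age at consent and consent pattern are not stated.
- **That naming MenC at 3 months contradicts section 3.1, where trial infants also receive it.** The phrase can be read as pointing to the product, where a real difference exists.
- **That no external infant had Bexsero at 12 months, or that every trial infant had all three doses.** The first rests on a list that omits Bexsero at every age; the second rests on a footnote describing the routine schedule.

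**Conclusion.** The concern holds in limited form. The stated justification for pooling omits a vaccine that the SAP's own text shows to differ, in presence for some external infants and in number of doses for others. The number affected is unknown; about 6 to 14 of 18 is an estimate that rests on even consent. The consequence is possible confounding of the SI2 control contrasts at 5 and 13 months by co-administered Bexsero. Its size cannot be derived from the SAP, and the planned check would miss most moderate differences. The randomised comparison and the primary endpoint are not affected. It should be corrected, because the remedy is cheap and the sentence carries the argument for pooling.

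**What to change.** In section 5:

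1. Rewrite the equivalence sentence so that it lists Bexsero (presence, number of doses and the 12-month dose) and the 3-month MenC product (Menitorix or NeisVac against NeisVac) as differences, and reconcile it with the footnote to section 3.1.
2. Tabulate recorded Bexsero doses for the 18 external infants.
3. Pre-specify, before data are seen, that the 5- and 13-month SI2 contrasts with controls are also reported with trial-recruited controls only, and with external infants shown by Bexsero status.

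The cost is SAP wording, retrieval of vaccination records for the earlier study, and a little extra analysis. The sensitivity analyses will have wider intervals: going from 48 to 30 controls widens the interval for the control mean by √(48/30) = 1.26, about 26%, and from 38 to 20 by √(38/20) = 1.38, about 38%.

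A strict rule admitting only external infants with the full trial Bexsero schedule is not recommended as the main analysis. It could leave few of the 18 at 5 months and possibly none at 13 months, which would defeat the purpose of section 5.

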### 6.2 Secondary end points

**SI1:** In the infant at birth (just vaccinated mothers group) - PT, PRN, FHA, FIM2, FIM3, TT (TT0.10/TT1.00) ,Dip (Dip0.10/Dip1.00).

**SI2:** In infants at 2,5 and 13 months (all groups) PT, PRN, FHA , FIM2, FIM3, Hib (Hib0.15, Hib1.00), TT (TT0.10/TT1.00) ,Dip (Dip0.10/Dip1.00), SBA (SBA8, SBA128), MenC, Polio1, Polio2, Polio3 (PolioX\_8), Pn\_x, Pn\_fun\_x.

**SM1:** In Mothers pre vaccination and at delivery (just vaccinated mothers group) - PT, PRN, FHA, FIM2, FIM3, TT (TT0.10/TT1.00) ,Dip (Dip0.10/Dip1.00).

**SM2:** In Mothers/Babies (cord blood) at delivery (just vaccinated mothers group) ratio of Baby to Mother PT, PRN, FHA, FIM2, FIM3, TT (TT0.10/TT1.00) ,Dip (Dip0.10/Dip1.00).

**SM3:** In Mothers (all groups) at 13 months: PT, PRN, FHA, FIM2, FIM3. (And for vaccinated mothers ratio with levels at delivery).

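### Section 5 drops meningococcal outcomes for the whole control group, contradicting SI2, although its reason applies only to the 18 external infants

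*SAP*

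**What the plan says.** **Objective SI2 (SAP 2.2, Infant)** includes "meningococcal serogroup C serum bactericidal antibody titres and meningococcal serogroup C-specific IgG concentrations" among the responses to be compared at 2, 5 and 13 months. The comparison is between the two vaccine groups "and compared to infants whose mothers who did not receive pertussis vaccination in pregnancy".

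**End point SI2 (SAP 6.2)** is set "In infants at 2,5 and 13 months (all groups"), and its list contains "SBA (SBA8, SBA128), MenC, Polio1, Polio2, Polio3". It makes no exception for controls.

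**SAP 3.1** applies one routine schedule to both rows of infants, with "3m: Infanrix/MenC (Neis)/Rotarix", and gives both rows the same bloods: BB at 2 months, BC at 5 months and BD at 13 months.

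**SAP 5** opens: "Due to the small size of the unvaccinated arm (control group), this will be increased by including results from babies of unvaccinated mothers". It lists Menitorix or NeisVacc as the MenC-containing vaccine of the external infants at 3 months, and bloods at 4, 5, 12 and 13 months. It reports that they had Bexsero only if born from May 2015, some of them as a catch-up. It then concludes: "Therefore vaccines are the same other than hepB added as Infanrix-hexa and MenC given at 3m", and continues: "For the control group Meningococcal outcomes will therefore not be assessed".

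**The concern.** The exclusion is attached to the wrong set of infants. A feature of the 18 added infants is used to remove an outcome from everyone in the unvaccinated group, including those enrolled and sampled under the trial's own schedule. An analyst who follows Section 5 leaves part of SI2 unreported. One who follows SI2 departs from Section 5 and, under SAP 1.3, must document a deviation. What is at stake is the only comparison in the plan that shows how infant MenC responses after maternal pertussis vaccination differ from those without it.

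**Working it through.** **1. Whom does the exclusion cover?** The opening sentence of Section 5 equates the unvaccinated arm with the control group. The later sentence uses the same term with no restriction to the added infants. Read literally, it covers in-trial and external controls alike.

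**2. To whom does the reason apply?**

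| | Infants of vaccinated mothers (SAP 3.1) | In-trial controls (SAP 3.1) | External infants (SAP 5) |
|---|---|---|---|
| MenC-containing vaccine at 3 months | MenC (Neis) | MenC (Neis) | Menitorix or NeisVacc |
| Blood at 2 months | yes | yes | none listed |
| Blood at 5 months | yes | yes | yes |
| Blood at 13 months | yes | yes | yes |

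The first two columns are identical. The 3-month difference lies only in the third column, and there only for infants given Menitorix. At 2 months the external infants contribute nothing, so that comparison could only ever use in-trial controls. Their sample is also scheduled before the 3-month dose. The stated reason therefore cannot support dropping it.

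**3. What is left out?** Two assays (SBA, also analysed at two thresholds, and MenC IgG) at three visits, in the control group only. The planned in-trial control group is 30, range 20 to 40 (SAP 4).

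**4. Would the retained comparison be informative?**

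Inputs from SAP 4: SD of log10 MenC SBA 0.50; 65 per vaccine arm; 20, 30 or 40 controls. The 5% level is from SAP 10.2. Two-sided testing and 80% power are assumptions, since the SAP states neither.

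Formula: fold = 10^[(1.960 + 0.842) × SD × √(1/n₁ + 1/n₂)].

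The plan's own figure first, 65 versus 65: √(2/65) = 0.1754; 2.802 × 0.50 × 0.1754 = 0.2457; 10^0.2457 = 1.76. SAP 4 states 1.77, so the figure is reproduced. At 90% power the result would be 1.92, so 80% is evidently what was used.

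One vaccine arm (65) versus in-trial controls:

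| Controls | √(1/n₁ + 1/65) | log10 fold | Detectable fold, 80% power | Power for a 2-fold difference |
|---|---|---|---|---|
| 20 | 0.2557 | 0.358 | 2.28 | 64% |
| 30 | 0.2207 | 0.309 | 2.04 | 77% |
| 40 | 0.2010 | 0.282 | 1.91 | 84% |

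The last column uses the noncentral t distribution with n₁ + 65 − 2 degrees of freedom and a difference of log10(2) = 0.301.

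**5. The comparability sentence.** It names two differences, hepB and MenC at 3 months. The text just before it reports a third: Bexsero depended on date of birth and was a catch-up for some, whereas SAP 3.1 lists it at 2, 4 and 12 months as routine. The summary is incomplete on the section's own facts.

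**The case against.** The strongest reply is that the authors probably meant only the added infants, that the control group is small and not randomised, and that one antigen family among many secondary outcomes is involved. The intention is plausible, but the text does not express it, and SI2 carries no matching exception. The point about importance stands and limits the severity.

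It can also be said that nothing is destroyed: samples and results remain, and the comparison between the two vaccine groups on SBA and MenC goes ahead. That is correct. The fault is an unanswered part of an objective, not a loss of data.

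Three stronger readings are tempting and should not be drawn.

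- A reader might infer that Menitorix at 3 months also makes Hib and tetanus results of the external infants non-comparable, so that pooling them inflates the control means. The SAP does not say what Menitorix contains, how many of the 18 received it, or how large any shift would be. It also makes pooling conditional on a comparison at p<0.005. The documents do not support the claim, or an exclusion rule built on it.
- A reader might infer that Section 5 wrongly implies that one study lacked a MenC dose at 3 months. The sentence reads naturally as saying that the MenC vaccine given then differed, which agrees with the two schedules.
- A reader might infer that the Bexsero difference was hidden or biases a retained antibody. Section 5 discloses it, and nothing in the SAP shows an effect on any retained outcome. Only the summary sentence needs correcting.

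**Conclusion.** The contradiction is real and is shown by the SAP's text alone. Section 5 removes SBA and MenC IgG for the entire unvaccinated group, SI2 requires them there, and the stated reason reaches only the 18 external infants. At 2 months it cannot apply at all.

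Keeping the in-trial controls would give a usable, though less sensitive, comparison: about 2.04-fold detectable (2.28 to 1.91 for 20 to 40 controls), against 1.77 stated between vaccine arms. This assumes that the planned numbers are evaluable, that testing is two-sided at 5% with 80% power, and that the post-primary SD of 0.50 holds; SAP 4 gives no SD for 2 or 13 months. Section 5 calls the unvaccinated arm small without giving its actual size, so sensitivity could be lower. The contradiction itself depends on none of these figures.

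The point should be fixed, but it is not critical. The primary end point (PT in infants of vaccinated mothers) and every REPEVAX versus BOOSTRIX-IPV comparison are untouched.

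**What to change.** Replace the exclusion sentence in Section 5 with wording such as: *SBA and MenC IgG will be analysed in the control group using only infants enrolled in iMAP2; the 18 Infanrix-Hexa study infants do not contribute to these analyses.* SI2 in 2.2 and 6.2 can then stand unchanged.

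Amend the comparability sentence so that it also names the Bexsero difference that the section reports.

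If the sponsor does intend to drop these outcomes for all controls, SI2 must be changed in both places and a reason given that applies to the in-trial infants.

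The cost is two sentences, with no new data or visits. The control group for these outcomes is then the in-trial infants alone (30 planned, range 20 to 40), with the detectable differences shown above. The change should be made before data reach the statistician, in line with SAP 1.3.

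### The rule for adding 18 external infants to the unvaccinated controls treats non-significance at p<0.005 as comparability, so it can rarely stop pooling at differences of the size the SAP targets

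*SAP*

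**What the plan says.** SAP section 4 plans 65 (+/-10) mother-infant pairs per vaccine arm, "with a control group of 30 (+/-10) women and their infants", that is 20 to 40 controls. Section 5 calls the control group small and adds infants of unvaccinated mothers from an Infanrix Hexa study ("18 babies consenting from 2014-January 2016"), tested in the same laboratory. Their pertussis, diphtheria, tetanus, Hib, polio and pneumococcal results "will be compared first between these 18 and the controls recruited in this study and only combined if differences are not significant at" p<0.005. The reason given for that level is "to allow for multiple comparisons".

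The external infants were bled at different times ("With bloods at 4m, 5m, 12m, 13m"), whereas endpoint SI2 (section 6.2) needs 2, 5 and 13 months in all groups. Section 5 also says: "Children will also have received Bexsero (at 2, 4m or in a 1 or 2 dose catch up) if born from May 2015". It then concludes that the vaccines are the same apart from the hepatitis B component and MenC at 3 months, and it drops meningococcal outcomes for the control group.

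Section 5 gives no similarity bound and no analysis restricted to the trial's own controls. It does not say whether pooling is decided per antigen and time point or once for all.

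**The concern.** The rule turns a failure to find a difference into permission to combine. A multiplicity correction protects against declaring a difference that is not there. Here that error only costs some precision, because 18 infants are left out. The harmful error is to miss a real difference and pool across it, and moving the threshold from 0.05 to 0.005 makes that error more likely.

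If the external infants are truly offset, the control geometric mean shifts towards them. The interval narrows around the shifted value, and nothing in the output warns the reader. With 20, 30 or 40 trial controls the external infants would be 18/38 = 47%, 18/48 = 37.5% or 18/58 = 31% of the pooled group.

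The SAP's own text gives reasons why an offset is possible. The routine schedule in section 3.1 has Bexsero at 2, 4 and 12 months, while the external infants received it only if born from May 2015. The 3-month MenC dose is NeisVac in section 3.1, but either Menitorix or NeisVac in the external study. The summary sentence on vaccine sameness leaves out Bexsero, so sections 3.1 and 5 must be reconciled.

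**Working it through.** **Inputs.** Log10 SDs from SAP section 4: "PT = 0.28, Hib = 0.76, MenC SBA = 0.50, Tet = 0.37". Planned folds from the same section: "with 65 per study arm fold differences of 1.38, 2.37, 1.77 and 1.52 would be detectable between the vaccine arms". There are 18 external infants and m = 20, 30 or 40 trial controls. The pooling threshold is 0.005 (section 5), the group-comparison level is 5% (section 10.2), and the test is the t-test on log values (section 10.4). Assumed, because the SAP does not say: two-sided tests, 80% power behind the planned folds, and these SDs applying to both control sources.

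**1. The plan's own figures.** Detectable fold = 10^[(1.960 + 0.842) × SD × √(2/65)]. For PT: 2.802 × 0.28 × 0.1754 = 0.1376, or 1.37-fold. The noncentral-t version gives PT 1.38, Hib 2.38, MenC 1.77 and tetanus 1.52, against the stated 1.38, 2.37, 1.77 and 1.52. The planned figures reproduce.

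**2. Power of the pooling test at those folds.** Standardised difference d = log10(fold)/SD: PT 0.1399/0.28 = 0.50; tetanus 0.1818/0.37 = 0.49; Hib 0.3747/0.76 = 0.49. Noncentrality λ = d/√(1/18 + 1/m). Power = P(T > t at 0.9975 with 16 + m degrees of freedom), with T noncentral t.

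For PT with m = 30: λ = 0.4996/0.2981 = 1.676, critical value 2.949, power 11.5%.

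| Trial controls | PT 1.38 | Tetanus 1.52 | Hib 2.37 |
|---|---|---|---|
| 20 | 8.8% | 8.5% | 8.5% |
| 30 | 11.5% | 11.0% | 11.1% |
| 40 | 13.4% | 12.8% | 12.9% |

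A real difference of this size would therefore be pooled about 87% to 91% of the time.

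**3. Where the test does work.** For 18 vs 30, 80% power needs d = 1.137, which is 2.08-fold for PT, 2.63-fold for tetanus and 7.31-fold for Hib. A true 2-fold difference is detected with 74% power for PT, 42% for tetanus and 6% for Hib.

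**4. A looser threshold.** At 0.05 the power for the same folds is 31% to 41% over 20 to 40 controls, so changing the level does not rescue the rule.

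**5. Effect on the control comparison.** Simulation, 40,000 runs per case, one antigen: 65 vaccinated infants against controls formed by the rule, no true difference between the vaccinated arm and the trial's own controls, external infants offset by an assumed amount. Ranges run from 40 to 20 trial controls.

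| Assumed offset | Pooled | Type I error at nominal 5% |
|---|---|---|
| 0 | over 99% | 5% |
| 0.25 SD | 98% | 7–9% |
| 0.5 SD | 86–91% | 13–20% |
| 0.63 SD (PT 1.5-fold: 0.1761/0.28) | 75–83% | 15–26% |

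At 0.5 SD with 30 controls, the control log-mean is biased by 0.5 × 18/48 = 0.19 SD when pooled and by 0.14 SD averaged over all runs. The average bias is about 1.10-fold for PT (10^(0.144 × 0.28)) and 1.29-fold for Hib (10^(0.144 × 0.76)).

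**6. Which comparisons are exposed.** The primary endpoint (section 6.1) and SI1, SM1 and SM2 use vaccinated mothers or their infants only. SM3 compares mothers, and only infant results are added. Meningococcal outcomes are dropped for controls. The external study has no 2-month blood. What remains is SI2 at 5 and 13 months for the other antigens, vaccinated arms against control.

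**The case against.** The defence has real substance. The same laboratory was used, the external mothers were also unvaccinated, and the schedule and Bexsero differences are disclosed. The outcomes most directly affected by the MenC difference are removed. The MenC exception in the summary sentence can be read as covering the choice of product. The trial's own controls are recruited postnatally and not randomised, so the 5% benchmark already assumes an exchangeability that the design does not guarantee. No randomised comparison is touched. Pooling also gains some precision.

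A reader might infer three stronger things that the documents do not support.

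- **That every control comparison is biased.** Step 6 shows that most endpoints, and all 2-month and maternal comparisons, are outside the rule's reach.
- **That the 18 infants are known to be non-comparable.** The SAP gives reasons why antibody levels might differ but no evidence that they do or by how much. With no offset the rule does no harm to type I error.
- **That the test is blind to any difference.** It would probably catch a 2-fold PT difference. Its weakness is at about half an SD.

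The figures are also for one test on one antigen. If pooling were decided once across many antigens, there would be more chances to refuse it. The SAP does not say which is meant.

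These points limit the scope and severity. None of them makes non-significance evidence of similarity, or makes a lower threshold the cautious choice.

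**Conclusion.** The point stands in a limited form. The stated reason for p<0.005 works in the wrong direction. Within the planned 20 to 40 controls, the check has 8.5% to 13.4% power against the differences that the SAP itself uses to size the trial. How much harm follows depends on an offset that the documents do not give: from none at zero offset to a type I error of 15–26% at a 1.5-fold PT offset. Bias is therefore possible rather than shown.

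Exposure is confined to the infant 5- and 13-month non-meningococcal SI2 comparisons with controls. The result rests on two-sided tests, on the quoted post-primary SDs applying to both control sources (including at 13 months), and on pooling decided test by test. The SAP gives no SDs for the other pertussis antigens, diphtheria, polio or pneumococcal serotypes, so the figures for those antigens are not known. This is a supporting secondary comparison: it should be fixed, but it does not threaten the trial's main result.

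**What to change.** In SAP section 5, delete the significance check. Make the concurrently recruited controls the main comparator for every SI2 comparison with controls. At 5 and 13 months, report the pooled group (concurrent plus the 18) as a labelled sensitivity analysis, beside the concurrent-to-external geometric mean ratio with its 95% CI for each antigen. State that 2-month comparisons use concurrent controls only. Reconcile the statement on vaccine sameness with the schedules in sections 3.1 and 5. Source adjustment, down-weighting or a prespecified similarity bound would also be defensible, but each needs more specification.

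The cost is wording, one extra set of tables, and somewhat wider intervals in the main control comparison. Detectable fold at 80% power, two-sided 5%, with 65 vs 30 instead of 65 vs 48:

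| Antigen | Concurrent only | Pooled |
|---|---|---|
| PT | 1.50 | 1.41 |
| Tetanus | 1.70 | 1.58 |
| Hib | 2.98 | 2.56 |
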